### Primary outcome

The primary outcome is a composite endpoint consisting of the time to first flatus and the time to first defecation [34], which are defined as the time from the end of the operation to the first exhaust and defecation, respectively, and will be recorded in hours in the case report form by patients under the supervision of an assessor during hospitalization. The minimum clinical significance of the primary outcome is 12 h [27].

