### Sample size

The primary outcome consists of the time to first flatus and the time to first defecation. Based on previous trials [24, 25] and clinical experience, the time to first flatus will be assumed to be 48 h and 64.8 h for the EA group and the control group, respectively, with a standard deviation of 21.6. Given a 2.5% two-sided significance, 80% power, and 10% drop rate, a sample size of 105 patients will be recruited, with 35 patients in each group. The time to first defecation will be assumed to be 86 h and 122 h for the EA group and the control group, respectively, with a standard deviation of 45. Given a 2.5% two-sided significance, 80% power, and 10% drop rate, a sample size of 90 patients will be recruited, with 30 patients in each group. In conclusion, 105 patients, with 35 patients in each group, will be recruited.

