### Statistical analysis

All statistical analyses will be performed according to the intention-to-treat (ITT) principle, which includes patients who will have received electroacupuncture at least once or who will have completed DSF for at least 1 day.

All paper data will be input into the electronic CRF and analyzed by SPSS 20. Measurement data will be presented as the mean ± standard deviation (M ± SD) or median and quartile spacing, and counting data will be presented as the composition ratio and percentage. Demographic and other baseline data will be compared by ANOVA and the chi-square test. The primary outcome and the time endpoints of the secondary outcomes will be compared by the Kaplan-Meier Breslow (generalized Wilcoxon) test. The incidence of pain, nausea, and abdominal distension; the frequency of vomiting; and the incidence of complications will be analyzed by the chi-square test or Mann-Whitney *U* test. Factors that may affect the results such as the stage and metastasis of colorectal will be recorded in the baseline. If these factors are unbalanced at baseline, we will use these factors as stratification factors to control the potential influence. The statistically significant *P* test level will be less than 0.025 for the primary outcome and less than 0.05 for the secondary outcomes. The primary outcome will be considered to be statistically different when both the first flatus time and the first defecation time are statistically different between the groups. The missing data will be filled using the last observation carry-over method. No additional, subgroup or interim analyses are planned for the trial.

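### Last observation carried forward is applied to all missing data, but it has no valid meaning for the first-event times that the plan compares by Kaplan-Meier and Breslow

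*Protocol article*

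**What the plan says.** All references are to the protocol article; no separate SAP is shown.

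- **Missing data** (Statistical analysis): "The missing data will be filled using the last observation carry-over method". No outcome is exempted.
- **Test** (Statistical analysis): "The primary outcome and the time endpoints of the secondary outcomes will be compared by the Kaplan-Meier Breslow (generalized Wilcoxon) test".
- **Primary outcome** (Primary outcome): two times, "defined as the time from the end of the operation to the first exhaust and defecation, respectively". Each "will be recorded in hours in the case report form by patients under the supervision of an assessor during hospitalization".
- **Success rule** (Statistical analysis): the primary outcome counts as different "when both the first flatus time and the first defecation time are statistically different between the groups". The level is also fixed there: "The statistically significant *P* test level will be less than 0.025 for the primary outcome".
- **Expected loss** (Sample size): "Given a 2.5% two-sided significance, 80% power, and 10% drop rate, a sample size of 105 patients will be recruited".

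Three other statements bear on who will lack an event time. Secondary outcomes has patients with serious complications discontinue. Data management follows patients who stop treatment for as long as possible, but no later than discharge. Statistical analysis keeps in the analysis set anyone with one electroacupuncture session or one day of the daily form. Censoring is not mentioned anywhere.

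**The concern.** Carrying a value forward needs a repeated measurement. Time to first flatus and time to first defecation are each a single number per patient, and until the event happens there is no earlier value of that number. For a patient who leaves first, the rule gives no answer, and the analyst has to invent one. There are at least two candidates:

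1. Enter the last observed time as the event time. A patient who has not recovered is then scored as having recovered at the moment of leaving.
2. Carry a daily not-yet status to the end of follow-up. The patient then stays event-free for longer than anyone observed.

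These push the result in opposite directions, and the sentence allows either to be chosen after the data are seen. Neither is needed, because Kaplan-Meier and the Breslow test use such a patient's event-free time up to last contact and then censor. So the plan states a filling rule that does not fit its own primary analysis. The stakes are power on both primary endpoints and, if exit differs between arms, bias in the comparison.

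**Working it through.** **1. The plan's own figure.** Inputs from Sample size: flatus means 48 h and 64.8 h (difference 16.8 h), SD 21.6 h, two-sided 0.025, power 80%, loss 10%.

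n per group = 2 (z₀.₉₈₇₅ + z₀.₈₀)² (SD/difference)² = 2 (2.241 + 0.842)² (21.6/16.8)² = 31.4. Dividing by 0.9 gives 34.9, so the stated 35 reproduces (rounding up to 32 first gives 36). For defecation (86 h and 122 h, SD 45 h) the same formula gives 29.7, that is 30 before loss and 33 to 34 after it; the final 35 covers this.

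**2. How far one mean can move.** If a share p leaves at time x and x is entered as the event, the arm's mean falls by about p × (mean − x). For 10% of controls:

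| Endpoint | Leaving at 24 h | Leaving at 48 h |
|---|---|---|
| Defecation | 0.1 × (122 − 24) = 9.8 h | 0.1 × (122 − 48) = 7.4 h |
| Flatus | 0.1 × (64.8 − 24) = 4.1 h | 0.1 × (64.8 − 48) = 1.7 h |

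The protocol's smallest important difference is 12 h.

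**3. Power with equal exit.** Simulated Breslow test, 35 v 35, two-sided 0.025, normal times with the plan's means and SDs. Assumed: 10% of each arm leave at 24 to 72 h, discharge at 168 ± 36 h, and correlation 0.5 between the two times.

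| | Leavers censored | Last time entered as event |
|---|---|---|
| Flatus | 79% | 75% |
| Defecation | 79% | 68% |
| Both (the success rule) | 67% | 57% |

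The direction does not depend on the normal shape. With gamma-distributed times and no discharge limit, power went from 86% to 82% (flatus) and from 88% to 79% (defecation).

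**4. Where the loss comes from.** At an assumed discharge of 168 h, the plan's figures leave (168 − 122)/45 = 1.02 SD, or 15% of controls, without defecation, and (168 − 86)/45 = 1.82 SD, or 3% of electroacupuncture patients. With discharge as the only cause of missing times, defecation power was 82% censored and 80% with the last time as event. Nearly all the damage comes from early leavers.

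**5. Unequal exit.** All exit rates here are assumed.

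- *No true effect, 15% v 5% leaving.* Taking the last time as the event, type I error for a single endpoint is about 4% (flatus) and 6% (defecation) against 2.5%. For both endpoints in the same direction it is 0.3%, 1.1% and 2.4% at correlations 0, 0.5 and 0.8; censoring gives 0%, 0.2% and 0.9%.
- *No true effect, 20% v 5% leaving (gamma times).* A false difference of about 11 h (defecation) and 3 h (flatus) appears, in favour of the arm losing more patients.
- *True effect, 5% electroacupuncture v 15% control leaving.* Defecation power falls from 80% to 46%, and power on both from 68% to 37%.

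**The case against.** **The rule may be meant only for the daily items.** The daily form yields repeated scores, for which a last observation exists, and naming Kaplan-Meier implies censoring. That may be the intention, but the sentence covers missing data in general, sits in the section that sets the primary analysis, and is not offset by any mention of censoring.

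**Censoring detail belongs in the SAP.** An omission could be left there. This is a stated rule that conflicts with the stated method, so it needs correcting where it stands.

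**Loss will be small.** These are inpatients, and collection continues on the ward after treatment stops. This stands in part: 10% gone by 24 to 72 h is a pessimistic case. But the plan itself budgets for 10% loss, and exit for serious complications can be related to bowel recovery.

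**Stronger readings that do not hold.** A reader might infer that the plan turns early leavers into early recoverers. The document never says that the last time becomes the event time; that is one of two readings. A reader might also infer that type I error for the primary outcome exceeds 2.5%. The 4% to 6% figures are for one endpoint under assumed unequal exit. Success requires both endpoints, and that rate stayed at or below about 2.5% in the 15% v 5% case. Nor does the point extend to how daily pain scores should be modelled, which is a separate matter.

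**Conclusion.** The point holds as a misfit between a stated rule and the stated primary analysis: last observation carried forward is undefined and invalid for both primary endpoints and for the secondary time endpoints. That conclusion rests on the text alone.

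The size depends on the reading and on assumptions. If the last time is entered as the event and 10% per arm leave at 24 to 72 h, the chance of meeting the success rule drops by about 10 percentage points (67% to 57%), mostly through defecation. Under equal exit the harm is lost power; bias between arms needs unequal exit. Exit timing, exit imbalance, discharge near 168 h and the correlation between endpoints are all assumed, since the protocol gives only an overall 10% drop rate. A type I error above 2.5% for the two-endpoint primary outcome is not shown.

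**What to change.** In Statistical analysis:

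1. State that last observation carried forward is not used for any time-to-event endpoint, primary or secondary.
2. State that a patient without the event is right-censored at the last documented assessment or at discharge, whichever ends that patient's observation.
3. Because exit for complications may be related to recovery, add one sensitivity analysis for those patients, for example censoring them at the longest follow-up in the trial.
4. If the rule is kept for the repeated daily measures, name the measures to which it applies.

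Cost: a few sentences and slightly more analysis work. No new data and no change in sample size. The wording should be settled before any outcome data are examined by arm.

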## Discussion

POI is a pathological state that always occurs after colorectal surgery and inflicts a considerable financial burden on patients and society. This trial will evaluate the effects of performing EA at ST25 or ST36 in accelerating the POI recovery time.

Although several trials have been conducted, the consensus [19] is that acupuncture is not a recommended treatment for POI, which may be due to the low reliability of trials. This trial fully meets methodological requirements and achieves full randomization of patients and blinding for patients, hospital staffs, outcome assessors and statisticians.

Actual clinical results show that postoperative patients are more likely to accept acupuncture with fewer acupoints, which can reduce the discomfort caused by acupuncture. Thus, we have chosen ST25 or ST36 as treatment acupoints, which have already been proven to be effective for gastrointestinal dysfunction [35–37]. Our aim is to observe whether EA at a single acupoint can promote recovery from POI.

The pathological state of POI lasts for a maximum of 4 days after surgery [33]. Our intervention will last for 4 days after surgery to ensure that every patient is treated with electroacupuncture during the pathological state. In addition, EA with 2/100-Hz stimulation has been proven to be effective in reducing postoperative incision and visceral pain [38, 39].

A limitation of the trial is that visible acupoints in patients in the two groups receiving acupuncture may break blindness. Another limitation is that as all patients will receive RSPC which is based on a protocol for enhancing recovery after surgery [40], it may lead to a ceiling effect, and the efficacy of electroacupuncture may be negatively affected. However, we hope the trial will provide more reliable evidence than previous studies and clarify the value of electroacupuncture as a treatment for POI.

## Data Availability

The generated and analyzed datasets for the study will be publicly available from the corresponding author on reasonable request. The results will be published in peer-reviewed international journals.
